#### Analysis of secondary outcomes

Between-group comparisons will be undertaken, including for the following key secondary outcomes:

Biochemically verified point prevalence abstinence at 3, 9 and 15* months post-baseline.Self-reported point prevalence abstinence at 3, 9 and 15* months post-baseline.Prolonged biochemically verified abstinence over 6 months between 9 and 15 months post-baseline.Prolonged biochemically verified abstinence for at least 12 months between 3 and 15 months post-baseline (derived from biochemically confirmed abstinence at all three follow-up time points).At least a 50% reduction in reported smoking levels between (1) baseline and 3 months, and (2) baseline and 9 months.Number of cigarettes used on an average day over the past week (including equivalent cigars, tobacco) at 3, 9 and 15* months post-baseline.Total number of LNCP used on an average day over the past week at 3, 9 and 15* months post-baseline.Total number of self-reported minutes engaged in MVPA over the past week at 3 and 9 months post-baseline.BMI at 3 and 9 months post-baseline.

NB: * only for those with biochemically confirmed abstinence at 9 months.

The following data are derived from accelerometers mailed to a subgroup of participants in both arms of the trial along with the 3-month questionnaire, which are returned after the accelerometers have been worn for 7 days:

The average time spent in moderate to vigorous activity over the past week.The average daily time spent sleeping over the past week.

No adjustment for multiple analyses will be made; such adjustment methods are too conservative when outcomes are positively correlated, as they would be in this trial. Analyses will use multivariable linear regression (continuous outcomes) or logistic regression (binary outcomes) to compare each of these secondary outcomes between allocated groups, with adjustment for site as a factor, and HSI, as an ordinal variable, as well as baseline values of the outcome as appropriate. As accelerometer data were only available at 3 months, only summary statistics for weekly minutes of MVPA shall be presented by allocated group without adjustment for baseline variables.

The between-group comparisons of continuous outcomes will be reported as mean differences together with 95% CIs, unless the outcomes are substantially skewed. Both adjusted and unadjusted differences will be presented. The between-group comparisons of binary outcomes will be reported as the adjusted and unadjusted ORs with conversion to relative risks and corresponding CIs, along with the absolute between-group differences in abstinence rates.

Analyses will be undertaken to investigate whether any effect of the intervention in terms of reduction in smoking at 3 months and 9 months is modified by key sociodemographic and/or behavioural factors at baseline. These prespecified factors at baseline are using smoking management medication or vaping, IMD, the stratification variables, MVPA level and confidence to quit. The multivariable models will be extended to include the interaction term of allocated group and each of the potential modifying variables.

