## Aims & objectives

The overarching aim of the trial is to determine if an individually tailored behavioural intervention for smokers wishing to reduce but not immediately quit provides an effective and cost-effective approach to supporting increases in PA and smoking reduction, resulting in increased rates of quit attempts and subsequent 6-month prolonged smoking abstinence.

The specific aims of the trial are to determine whether the intervention, compared with support as usual (SAU), will:

Increase the proportion of participants who achieve 6-month prolonged biochemically verified floating abstinence at 9 months post-baseline.Increase the proportion of participants who self-report a reduction in number of cigarettes smoked (between baseline and both 3 months and 9 months) of at least 50%.Increase the proportion of participants who achieve biochemically verified prolonged abstinence at 15 months post-baseline (ie, 12 months post-intervention).Increase self-reported PA at 3 and 9 months post-baseline, and accelerometer assessed PA at 3 months post-baseline.Improve quality of life, self-reported weight and cigarette cravings at 3 and 9 months post-baseline.

Further aims are:

To conduct a health economic evaluation to estimate the costs of delivering the intervention and differences in health and social care costs between intervention and SAU at 9 months post-baseline. This will also estimate the cost-effectiveness of the intervention compared with SAU at (1) 9 months and (2) over a longer term/lifetime horizon.To conduct an embedded mixed-methods process evaluation to explore the mechanisms of action of the intervention and acceptability of study processes.

The current paper outlines the protocol for the Trial of physical Activity-assisted Reduction of Smoking (TARS) trial.

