#### Baseline assessment

Participants then completed a baseline questionnaire with a member of the local study team either face-to-face, by mail or over the telephone. The schedule of measures and data collection at baseline and follow-up are shown in table 1.

**Table 1 T1:** Schedule of baseline and follow-up measures

	Screening and baseline	Month 3	Month 9	Month 15*
Demographics (eg, age, gender, education attained, employment status)	**X**			
Self-reported cigarettes per day (or equivalent)	**X**	**X**	**X**	**X**
Reduction of ≥50% in number of cigarettes smoked since baseline†		**X**	**X**	
Biochemically confirmed abstinence (self-reported quitters only)		**X**	**X**	**X**
Self-reported floating prolonged abstinence (since quitting smoking, with quit date, if relevant) over at least 6 months†			**X**	**X**
Accelerometer assessed minutes of moderate and vigorous physical activity in a subsample		**X**		
Self-reported 7-day recall of physical activity	**X**	**X**	**X**	
Heaviness of Smoking Index	**X**			
Use of smoking management products	**X**	**X**	**X**	**X**
Urge and strength of urge to smoke	**X**	**X**		
Engagement with the health trainer intervention (8 weeks, plus optional 6 weeks additional support if a quit attempt is made)		**X**		
Health and social care utilisation	**X**	**X**	**X**	
Health-related quality of life (EQ-5D-5L and SF-12)	**X**	**X**	**X**	
Self-reported weight and height (to calculate BMI)	**X**	**X**	**X**	
Self-reported process measures	**X**	**X**		
Importance and confidence in smoking reduction and cessation				
Importance and confidence in being physically active				
Action planning to change smoking				
Action planning to change physical activity				
Self-monitoring of smoking				
Self-monitoring of physical activity				
Availability of support to reduce smoking				
Availability of support to increase physical activity				
Use of physical activity for smoking regulation				
Serious adverse events (self-reported)		**X**	**X**	
Qualitative process evaluation (in parallel throughout) (sample)	**X**	**X**	**X**	**X**

*Only participants with biochemically verified abstinence at 9 months are followed-up at 15 months post-baseline.

†Derived measure.

BMI, body mass index; EQ-5D-5L, EuroQol-5 dimension-5 level; SF-12, 12-Item Short Form Health Survey.

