### Determination of sample size

Since the planned primary analysis is a comparison of the proportions of the binary primary outcome, the sample size calculation was based on a two-sided Fisher exact test. An abstinence rate of 5% for the control group and detectable effect of 6% (ie, an increase from 5% to 11% due to the intervention) are conservative estimates consistent with those from the EARS pilot study^15^ and those reported from a systematic review of pharmacological interventions.^38^ The corresponding OR for this effect size is 2.35. Participants with missing outcome data will be assumed to be still smoking following the Russell Standard,^39^ and the numbers of participants in each allocated group are assumed to be in the ratio of 1:1. Under these conditions, according to Stata V.14.2, the minimum number of participants required to detect an abstinence rate of 11% compared with that of 5% in the control group, with a significance level of no more than 5% and power of at least 90%, is 900, above which a power in excess of 90% is maintained.

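### Four 15-month secondary comparisons are restricted to participants verified abstinent at 9 months, a subset formed after randomisation by an outcome the intervention is meant to change

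*Protocol article*

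**What the plan says.** The section Analysis of secondary outcomes lists outcomes for between-group comparison. Four carry an asterisk on their 15-month assessment: verified point prevalence abstinence, self-reported point prevalence abstinence, cigarettes per day and licensed nicotine-containing products (LNCP) per day. One of these reads "Number of cigarettes used on an average day over the past week (including equivalent cigars, tobacco) at 3, 9 and 15* months post-baseline". The note to the asterisk reads "only for those with biochemically confirmed abstinence at 9 months". The section then assigns linear or logistic regression by allocated group to the listed outcomes.

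The restriction also governs data collection. The footnote to Table 1 (under Baseline assessment) states: "Only participants with biochemically verified abstinence at 9 months are followed-up at 15 months post-baseline". Other smoking-related measures says the same about who is contacted.

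Two further 15-month outcomes have no asterisk: prolonged verified abstinence from 9 to 15 months and from 3 to 15 months. The 15-month aim in Aims & objectives is to raise the proportion of participants who "achieve biochemically verified prolonged abstinence at 15 months post-baseline". The rule that participants with missing responses count as smokers on an intention-to-treat basis is stated under Primary analysis, for the primary comparison.

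**The concern.** Verified abstinence at 9 months is something the intervention is designed to produce. If it works, the intervention arm's 9-month abstainers include people who would still be smoking had they been allocated to control. Within the subset, the arms therefore differ in the kind of person they contain, and randomisation no longer protects the comparison. What is estimated is relapse among differently selected quitters, not the effect of allocation on smoking at 15 months.

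Two consequences follow. An intervention that raises quitting and leaves relapse unchanged would show no effect on these outcomes, and one whose additional quitters relapse somewhat more often would appear harmful. The point-prevalence label also does not fit, because anyone who stops smoking after month 9 is never contacted and cannot be counted.

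**Working it through.** **The plan's own figures.** Determination of sample size takes 5% abstinence in control and 11% in the intervention arm, and says "The corresponding OR for this effect size is 2.35". Check: (0.11/0.89) / (0.05/0.95) = 2.348, which agrees. The total "with a significance level of no more than 5% and power of at least 90%, is 900" also reproduces: the exact power of the two-sided Fisher test is 0.9003 at 450 per arm and 0.8995 at 449.

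**Inputs to the illustration.**
- Verified abstinence at 9 months: a_C = 0.05 and a_I = 0.11. These are the planning rates for the primary outcome (prolonged abstinence over months 3 to 9), used here as an assumption for 9-month verified abstinence. The true subset may be larger, because people who quit after month 3 and are verified at month 9 also belong to it.
- Retention of abstinence from 9 to 15 months: r = 1 − relapse. The documents give no value, so r is assumed and varied.

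**Size of the subset.** 450 × 0.05 = 22.5 and 450 × 0.11 = 49.5, together 72 of 900, or 8%.

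**Formulas.** The subset comparison sets r_I against r_C. The all-randomised comparison sets a_I × r_I against a_C × r_C. In risk ratios, the all-randomised value is (a_I/a_C) × (r_I/r_C), whereas the subset gives r_I/r_C alone. Restriction thus removes the factor a_I/a_C, which is the effect on quitting by month 9 (0.11/0.05 = 2.2 here).

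| Assumed relapse, control vs intervention | Subset: still abstinent | Subset OR | All randomised: abstinent | All-randomised OR |
|---|---|---|---|---|
| 30% vs 30% | 70% vs 70% | 1.0 | 3.5% vs 7.7% | 2.30 |
| 30% vs 40% | 70% vs 60% | 0.64 | 3.5% vs 6.6% | 1.95 |
| 20% vs 40% | 80% vs 60% | 0.375 | 4.0% vs 6.6% | 1.70 |

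Worked for the first row: (0.077/0.923) / (0.035/0.965) = 2.30. Worked for the last row: subset (0.6/0.4) / (0.8/0.2) = 0.375; all randomised (0.066/0.934) / (0.040/0.960) = 1.70.

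**When the direction reverses.** The subset points against the intervention while the all-randomised result favours it whenever r_I/r_C lies between a_C/a_I = 0.05/0.11 = 0.45 and 1. With 70% retention in control, that means any intervention retention between about 32% (0.70 × 0.05/0.11 = 0.318) and 70%.

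**The unstarred outcomes.** Prolonged abstinence over 9–15 and over 3–15 months both require verified abstinence at 9 months by definition. Anyone not verified then is a known failure, so all randomised participants can be the denominator although only the abstainers are followed.

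**The case against.** The best counter-argument is that the asterisk says who is measured, not who is in the denominator. It echoes the Table 1 footnote, which concerns follow-up. The comparisons are described as between allocated groups, and absolute differences in abstinence rates are promised. On that reading, participants not followed at 15 months would count as smokers, and the detailed rule could sit in the analysis plan, which is not shown.

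This has force for the two point-prevalence outcomes. The article does not say it, however: the missing-equals-smoking rule is written for the primary comparison, and the note as worded restricts the outcomes. Even under the kinder reading the label remains wrong, since quitting after month 9 cannot be observed. For cigarettes and LNCP per day the argument fails, because no 15-month values exist outside the subset and any regression between arms is conditional on 9-month abstinence.

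A second objection is that the illustration rests on assumed relapse and on planning rates for a different abstinence measure. That is correct, and the odds ratios are examples, not predictions. A larger subset would change the figures but would not remove the selection.

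A reader might also infer that every 15-month comparison, and with it the 15-month aim, is compromised. The documents do not support this. The two prolonged-abstinence outcomes carry no asterisk, can be analysed on all randomised participants without loss from the restricted follow-up, and are the ones that serve the aim.

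**Conclusion.** The point holds for the four starred 15-month outcomes. For cigarettes and LNCP per day it holds on any reading; for the two point-prevalence outcomes it holds as the text is written, and stating the denominator would settle it. Under the assumptions shown, a true all-randomised odds ratio of 2.30 becomes 1.0 in the subset when relapse is equal, and 1.70 becomes 0.375 when relapse is 20% in control and 40% in the intervention arm. The figures depend on setting 9-month verified abstinence to 5% and 11% and on assumed relapse; the direction of the problem depends only on the intervention affecting abstinence at 9 months.

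The primary outcome, its analysis, the sample size of 900, the unstarred prolonged-abstinence outcomes and the 15-month aim are not affected. Severity is moderate: listed secondary outcomes could report no effect or apparent harm where the randomised comparison shows benefit.

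**What to change.** For the two starred abstinence outcomes, state that the denominator is all randomised participants and that anyone not verified abstinent at 9 months counts as not abstinent at 15 months. Relabel them as verified abstinent at 9 months and verified abstinent at 15 months, and as verified abstinent at 9 months and self-reported abstinent at 15 months, respectively.

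For cigarettes and LNCP per day at 15 months, replace the between-group regression with descriptive summaries by arm, labelled as coming from a subset selected on outcome.

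This is a change of wording in the analysis plan and needs no new data. The cost is that two 15-month comparisons become descriptive. The relabelled outcomes still say nothing about quitting after month 9, which the follow-up design cannot capture.

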#### Self-reported process measures

Single-survey items, using a 5-point Likert scale (strongly disagree to strongly agree) assessed the psychological and behavioural processes that the intervention was designed to influence as shown in table 2. These were used in other trials.^15 48 49^ A single-survey item, using a 6-point scale (not at all to all the time), was used to assess frequency of urge to smoke in the past week.^50^ A single survey item (6-point Likert scale, no urges to extremely strong) assessed strength of urges to smoking in the past week^50^ as used previously.^15^

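### Accelerometer-assessed activity is a comparative aim, but the plan gives it group summaries only, with no between-group estimate or confidence interval

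*Protocol article*

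**What the plan says.** **Accelerometer activity.** In the Protocol article, Aims & objectives introduces its list with "The specific aims of the trial are to determine whether the intervention, compared with support as usual (SAU), will". One item is "Increase self-reported PA at 3 and 9 months post-baseline, and accelerometer assessed PA at 3 months post-baseline". Under Follow-up, about 20% of participants were sent a wrist-worn device at 3 months. PA measures describes this as the objective measure of weekly moderate and vigorous activity (MVPA).

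Analysis of secondary outcomes sets a general rule: linear or logistic regression between allocated groups, adjusted for site and HSI, and for the baseline value of the outcome where appropriate. It then makes an exception. The reason is "As accelerometer data were only available at 3 months", and the consequence is that "only summary statistics for weekly minutes of MVPA shall be presented by allocated group without adjustment for baseline variables".

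**Cravings.** Another item in the aims is "Improve quality of life, self-reported weight and cigarette cravings at 3 and 9 months post-baseline". In Table 1 (Baseline assessment), the row "Urge and strength of urge to smoke" is marked at screening/baseline and at month 3. The month 9 and month 15 cells are empty. Self-reported process measures describes the item that "was used to assess frequency of urge to smoke in the past week", and a companion item on strength, but names no time points for either.

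**The concern.** The aim asks a comparative question, and the plan fixes an analysis that returns no comparison. Two group summaries side by side invite the reader to judge the difference informally, with no statement of its uncertainty.

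This outcome matters more than most secondary ones. The Blinding section says participants could not be blinded, and the intervention promotes activity, so self-reported MVPA is open to reporting that follows allocation. The accelerometer is the one activity measure free of that problem. The article also gives activity a central place in the proposed mechanism and in the planned mediation work, so whether activity changed at all deserves an estimate.

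The cravings point is of a different kind and smaller. An aim names a time point at which the schedule shows no measurement.

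**Working it through.** **Does the reason given support the choice?**

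1. Randomisation is individual and 1:1, so a comparison of a follow-up value alone is valid. A baseline value would improve precision but is not needed for validity.
2. The plan accepts this elsewhere. Table 1 schedules the abstinence measures only after baseline, yet Primary analysis and Analysis of secondary outcomes compare them by logistic regression adjusted for site and HSI.
3. The general rule uses baseline values only where appropriate, so it already accommodates an outcome that has none.
4. Under Blinding, devices were mailed out and returned without knowledge of allocation. Analysis of secondary outcomes says they went to a subgroup in both arms. Nothing there rules out a comparison within the subgroup.
5. Table 1 shows 7-day recall of activity collected at baseline, so a related baseline covariate is available if wanted.

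**What would a comparison deliver?** The plan gives no precision or power figure for this outcome. The only planned figure used here is the total of 900 from Determination of sample size. It reproduces: two-sided Fisher exact power for 5% versus 11% is 0.8995 at 449 per arm and 0.9003 at 450 per arm. That figure concerns the primary outcome and serves here only as a base.

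Inputs:
- Total 900 and ratio 1:1 (Determination of sample size).
- Fraction sent a device, about 20% (Follow-up): 0.20 × 900 = 180, or 90 per arm if split equally.
- Usable fraction: not stated. I assume 100%, 80% and 60% to show a range.
- Two-sided 5% level and 80% power, chosen for illustration.

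Formulas, in SD units, with n analysable per arm (normal approximation, unadjusted):
- 95% CI half-width = 1.96 × √(2/n)
- Detectable difference = (1.96 + 0.84) × √(2/n)

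| Usable fraction (assumed) | n per arm | CI half-width | Detectable difference |
|---|---|---|---|
| 100% | 90 | 0.29 SD | 0.42 SD |
| 80% | 72 | 0.33 SD | 0.47 SD |
| 60% | 54 | 0.38 SD | 0.54 SD |

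For example, at n = 90, √(2/90) = 0.149. Multiplying by 1.96 gives 0.29, and by 2.80 gives 0.42.

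**Cravings, side by side.** The aims say 3 and 9 months. Table 1 says baseline and month 3. The Mediational analysis section uses urges from baseline to 3 months, which agrees with Table 1 but does not settle whether the 9-month booklet also carried the items. No arithmetic applies.

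**The case against.** The best defence is that this is a disclosed choice for a small subsample in a trial sized only for its primary outcome. Summaries by arm are still planned. If means, SDs and numbers are given, a reader can work out an unadjusted difference and its CI. This has some force, since what is missing is a reported contrast and not all information on the arms. But Baseline characteristics and summary statistics says skewed data will be given as median and IQR. Weekly activity minutes may well be skewed, and a difference in means with its CI cannot then be recovered directly. Nor is small size the reason the article gives. It would be a reason to report a wide interval, not to omit one.

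Three stronger readings are tempting, and the document does not support them:

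- **That two aims cannot be answered.** Only part of each is affected. Self-reported activity is compared at 3 and 9 months. Urges are scheduled at 3 months, and quality of life and weight at both times.
- **That the analysis section contradicts itself by listing accelerometer outcomes under between-group comparisons.** That list ends at BMI and its footnote. The accelerometer items follow under a separate sentence that promises no comparison. The text reads as a general rule with an exception.
- **That no 9-month craving data exist.** The article shows only that the aim and Table 1 disagree, not which is right.

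Adjustment for baseline self-reported MVPA is optional; site and HSI already follow from the plan's own rule.

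**Conclusion.** The point holds for part of one aim. The trial sets out to determine whether accelerometer-assessed activity rises relative to support as usual, and the analysis as written yields no effect estimate or interval for it. The missing baseline value does not justify this, because the plan compares other outcomes that also have none.

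The achievable precision is modest: a CI half-width of about 0.29 SD at best, and 0.38 SD if only 60% of the data are usable. That would help to judge a moderate difference but would not exclude a small one. These figures rest on 900 participants, a 20% subsample split equally between arms, no covariate gain, and usable fractions that I assumed. The case for reporting an estimate does not depend on them.

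The cravings mismatch is real but minor. Both matters concern secondary outcomes, and the primary analysis is unaffected.

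**What to change.** Replace the exception in Analysis of secondary outcomes with wording to this effect: accelerometer MVPA at 3 months will be compared between allocated groups by linear regression adjusted for site and HSI, and reported as a mean difference with a 95% CI, bootstrapped if the distribution is skewed. Baseline self-reported MVPA may be added as a covariate if that is specified in advance. Report the numbers sent a device, returning it and analysable, by arm, and label the estimate as of limited precision.

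For cravings, check the 9-month questionnaire actually used. If urges were not collected, limit the aim to 3 months. If they were, correct Table 1.

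The cost is one regression, using methods the article already describes, and a few lines of wording. No new data are needed. The article says the analysis plan is to be approved before database lock, so on its own account the change can still be prespecified. If lock has already passed, the comparison should be reported as added afterwards.
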